#### Analysis of the Effectiveness

Analysis of the primary outcome (ie, functionality of the affected upper extremity) will be performed using the per-protocol principle. Treatment effects will be compared using a 2-way repeated ANOVA for clinical measurements, considering “time” (3 levels: T0, T1, and T2) as a within-subject factor and “group” (3 levels: EG@Hosp, EG@Home, and CG) as a between-subject factor.

In addition, the percentage of participants who passed the minimal clinically important differences of the FMA-UE will be compared using chi-square tests between the 3 groups.

The mean power across the assessment “time” (ie, T0 and T2) related to the action observation condition will be implemented in a mixed-design ANOVA to evaluate significant changes. A separate ANOVA will be performed to assess power changes in the stimuli selection data, using “treatment” (ie, EG@Hosp vs EG@Home vs CG) as the between-subjects factor and action as the within-subjects factor. To assess the predictive value of biomarkers for AOT effectiveness, an analysis of covariance (ANCOVA) will be performed considering the clinical data as the dependent variable, the “group” as a fixed factor, and the biomarkers as covariates.

Subsequently, to evaluate kinematic parameters recovery, a mixed design ANOVA will be implemented with “time” and “treatment” as within- and between-subjects factors, respectively.

The level of significance will be set at *P*<.05. For post hoc comparisons, the level of significance will be set at *P*<.017 after Bonferroni adjustment (.05/n; the number of comparisons, n=3) for the comparison of interaction effects. Cohen *d* will be calculated to determine the effect size of the change in scores for the behavioral motor outcomes between the groups. Immediate training effects (data from T0-T2) and the durability of training effects (data from T2-T3) will be separately investigated using mixed effect models.

Clinical-neurophysiological correlations will also be analyzed: the correlation between the ERD and factors such as the clinical scale score will be studied. To evaluate the differences in trends related to the clinical evolution of the patients, we will define a new variable to group the participants according to the presence or absence of relevant clinical improvements. The relevant clinical improvement will be defined by a clinical specialist for this purpose.

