## Methods

### Overview

A randomized, parallel-arm, controlled, outcome measurer–blinded, and multicenter clinical trial conducted in 2 neurorehabilitation centers in Italy aims to investigate the effectiveness of AOT in patients with chronic stroke (ie, >6 months from the first event) using quantitative EEG biomarkers, confirming the translational power of a tailored treatment.

A total of 60 individuals who have been enrolled will be randomized to the experimental group in hospital (EG@Hosp), experimental group at home (EG@Home), or control group (CG) in a 1:1:1 ratio.

The EG@Hosp will observe and execute ADL that are task-oriented actions (AOT protocol); the EG@Home will observe and perform the same ADL at home (AOT protocol at home); and the CG will not observe any motor task videos (but will watch video only on landscapes and historical issues), and after verbal instructions, they will perform the same actions observed by the other 2 groups.

After completing the patient screening, randomization will be performed before the first treatment session (T0). At baseline (T0), midintervention (after the 7th session; T1), and after the intervention (15th session or 5th week; T2), outcomes (ie, clinical scales, EEG and electromyography [EMG] signals, and kinematic parameters) will be assessed to evaluate impairment and functional abilities.

For each group, the total duration of the intervention will be 5 weeks (3 times a week) for a total of 15 sessions. After the end of the intervention, a 2-month follow-up assessment period (T3) will be scheduled to assess the maintenance and long-term effects.

The primary outcome assessed at T2 will be assessed by the Fugl-Meyer Assessment-Upper Extremity (FMA-UE) scores.

The trials will be performed at 2 neurorehabilitation centers in Italy: IRCCS San Raffaele Roma Hospital in Rome and at Casa di Cura del Policlinico Hospital in Milan.

All the data will be recorded in electronic case report forms through the REDCap (Research Electronic Data Capture; Vanderbilt University) system, accessed on the web via the internet for data collection and management.

A specific route diagram is presented in Figure 1. The protocol for this study was developed in accordance with the Standard Protocol Items: Interventional Trial Recommendations guidelines (SPIRIT) [40].

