### Sample Size

As the changes in the effects of upper limb AOT in patients with stroke on EEG biomarkers have not been previously investigated, we have estimated the sample size based on previously published studies [58,59], comparing AOT and conventional therapy. We estimated the sample size required to detect differences in the effects of “group”×“time” interactions on primary clinical outcome (FMA-UE).

For this outcome, an effect size of 0.495 [60,61] is expected based on previous studies. Given the expected effect size, a total sample size of 54 will be required for repeated ANOVA with a power of 0.8 and a 2-sided type-I error of 0.05 (number of groups=3 [ie, EG@Hosp, EG@Home, and CG]; number of measurements=3 [ie, T1, T2, and T3]). Therefore, when considering a dropout rate of 10%, we plan to recruit 20 participants for each group (a total of 60 participants) for this study.

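### The primary outcome is analysed only per protocol, with no as-randomised analysis, so the group comparisons lose the protection of randomisation

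*Protocol article*

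**What the plan says.** The Overview of the Methods fixes the endpoint: "The primary outcome assessed at T2 will be assessed by the Fugl-Meyer Assessment-Upper Extremity (FMA-UE) scores". Sixty participants are allocated to hospital AOT, home AOT "or control group (CG) in a 1:1:1 ratio". The section Analysis of the Effectiveness then fixes the population: "Analysis of the primary outcome (ie, functionality of the affected upper extremity) will be performed using the per-protocol principle". The treatment comparison is a two-way repeated ANOVA over T0, T1 and T2 in three groups, with post hoc comparisons at .017. The same section plans mixed effect models for T0-T2 and for T2-T3, without saying which participants enter them.

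Four other places bear on this:

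- Patient Withdrawal Criteria lists absence from more than three consecutive sessions among the reasons for which a patient may stop the study. Patient request and organisational or personal reasons are on the same list.
- Blinding says that participants and those delivering treatment are not blinded; assessors are.
- The intervention sections place EG@Hosp and CG on hospital premises. EG@Home patients work on a tablet at home after training of patient and caregiver, with remote monitoring.
- Sample Size makes one overall allowance for losses: "when considering a dropout rate of 10%, we plan to recruit 20 participants for each group".

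The per-protocol set is not defined.

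**The concern.** Randomisation makes the three groups comparable at entry. That holds in the analysis only if everyone randomised is analysed as allocated. A per-protocol set is formed by events after allocation. Where participants and therapists know the arm, those events can depend both on the arm and on how the patient is doing. A difference in FMA-UE change between the remaining groups may then reflect who was left out as well as what treatment did.

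The trial presents itself as a test of effectiveness, and its ANOVA tests for a difference. The discussion hopes for comparable benefit at home, but no non-inferiority margin is set, so the usual reason for giving weight to a per-protocol analysis is absent. The second aim is the feasibility and impact of the home programme. Patients who could not keep to it carry information on that aim, and they are the ones most likely to be left out.

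**Working it through.** **1. The plan's own figure.** Sample Size gives three groups, three measurements and "an effect size of 0.495 [60,61] is expected based on previous studies", and concludes that "a total sample size of 54 will be required for repeated ANOVA with a power of 0.8 and a 2-sided type-I error of 0.05". The metric of 0.495 is not stated. One reading reproduces the number: a noncentral F test of the group-by-time interaction with df1 = (3-1)(3-1) = 4, df2 = 2(N-3) and λ = N × 0.495².

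- N = 51: λ = 12.50, df2 = 96, power 0.798.
- N = 54: λ = 13.23, df2 = 102, power 0.825.

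So 54 is the smallest total in equal arms that reaches 0.80, and 54 / 0.90 = 60. Other readings do not give 54; a one-way ANOVA with f = 0.495, for example, gives 45. The sample size is not in dispute here. The formula is reused in step 3.

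**2. What post-randomisation exclusion could do.** The article has no adherence or dropout by arm, so every input in this step except the 20 per arm is an assumption. Change in FMA-UE is in SD units, with no true effect. Adherence (or another prognostic factor that drives exclusion) is standard normal with correlation r to change. The lowest fraction p of an arm is removed.

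The mean change of those who remain shifts by r × φ(z_p)/(1-p). The factor φ(z_p)/(1-p) is 0.109 for p = 5%, 0.195 for 10%, 0.350 for 20% and 0.497 for 30%. The bias is the difference of the two arms' shifts. For 20% against 5%:

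- r = 0.3: 0.3 × (0.350 - 0.109) = 0.072 SD
- r = 0.5: 0.5 × (0.350 - 0.109) = 0.121 SD

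Type I error is Φ(-1.96+δ) + Φ(-1.96-δ), with δ = bias / √(1/n1 + 1/n2). This is a normal approximation with the SD held at 1. For 30% against none at r = 0.5, n1 = 14, n2 = 20, δ = 0.248/0.3485 = 0.71, and the error is 0.110.

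| Excluded, one arm v other | Bias in SD (r = 0.3 to 0.5) | Type I error at 0.05 | Type I error at 0.0167 |
|---|---|---|---|
| 10% v 10% | 0 | 0.050 | 0.017 |
| 20% v 5% | 0.07 to 0.12 | 0.055 to 0.065 | 0.019 to 0.024 |
| 30% v 10% | 0.09 to 0.15 | 0.057 to 0.071 | 0.020 to 0.027 |
| 30% v 0% | 0.15 to 0.25 | 0.071 to 0.110 | 0.027 to 0.047 |

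The bias favours whichever arm loses more patients. Nothing in the table depends on that arm being EG@Home or on the comparator being CG rather than EG@Hosp.

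**3. Power if all 60 are analysed as allocated.** The formula is that of step 1 with N = 60, df2 = 114 and λ = 60 × (0.495 × (1 - dilution))². Dilution is assumed, as is complete T2 data.

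| Dilution of effect | λ | Power |
|---|---|---|
| 0% | 14.70 | 0.869 |
| 5% | 13.27 | 0.828 |
| 10% | 11.91 | 0.780 |
| 15% | 10.62 | 0.725 |

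**The case against.** The strongest defence is that no harm is shown. If the arms lose patients equally and for the same reasons, the bias is zero. The article is condensed and leaves the per-protocol set undefined. Stopping after missed sessions is permitted rather than automatic, scattered absences do not trigger it, and investigators must try to retain patients. Outcome assessors are blinded. All of this stands, and it limits what can be said about size. It does not restore an as-randomised comparison. Blinded assessment protects the measurement, not the choice of who is analysed. Nor is this a detail left to an unseen analysis plan: the article states the principle, and a plan consistent with it would also be per-protocol for the primary outcome.

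The planned mixed effect models are a partial answer. They cover T0-T2, but the article does not say that they include everyone randomised.

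A reader might infer three stronger things that the documents do not support:

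- **Home versus control is biased most.** By the setting argument, home versus hospital AOT is equally exposed, since both comparators are treated on hospital premises.
- **The bias flatters the home arm.** Attending hospital three times a week for five weeks could cost the hospital arms as many patients or more. Home patients are not unsupported either: the plan provides caregiver training, scheduled sessions and remote monitoring.
- **Per-protocol exclusions will push the evaluable number below 54.** Patients who stop after missed sessions may already be counted in the 10% allowance. No separate non-adherence rate is given from which to compute a further loss.

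**Conclusion.** The concern holds in this form: the only stated analysis population for the primary outcome is per-protocol, in an unblinded-treatment trial that tests for a difference. This should be corrected before the arms are compared. Size and direction of the bias cannot be derived from the documents. The illustration runs from no bias under equal exclusion to about 0.25 SD, with type I error of about 0.11 at a nominal 0.05, under 30% one-sided exclusion and a correlation of 0.5. That upper end is a deliberately one-sided case. The milder 20% against 5% gives 0.07 to 0.12 SD and a type I error of 0.055 to 0.065. That comparisons with EG@Home may be the most exposed is a reasonable inference from the difference in setting, not a finding from data. The case for change rests on the principle stated in the plan, not on any one simulated value.

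**What to change.** Replace the per-protocol sentence in Analysis of the Effectiveness. The primary analysis of FMA-UE should include all randomised participants in the arm allocated, using a likelihood-based mixed model on every available score at T0, T1 and T2, with the group contrast at T2 as the target. Keep per-protocol as a sensitivity analysis, define the set in terms of sessions completed and protocol deviations, and report exclusions by arm with reasons. State which participants enter the T0-T2 and T2-T3 mixed models. No change to the rules for stopping treatment is implied.

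The cost is small. Mixed models are already planned, so only the population changes. The abstract reports recruitment closed and analyses still to be completed, so the change can be made as a dated amendment, provided the arms have not yet been compared. The real price is dilution by non-adherence: power stays above the planned 0.80 at 5% dilution (0.83) and falls slightly below it at 10% (0.78). The allowance for 54 evaluable patients covers losses but was not set to cover dilution. The mixed model also relies on missing scores being missing at random given the observed data, which should be stated.

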### Assessment: Instrumental Setup

The assessment setup and protocol will be the same as those used in similar studies [33,41] for the evaluation of impaired upper extremity functionality. The participant will sit in front of a target panel (eg, a 24-inch touch screen monitor) to perform the pointing task evaluation test.

The panel will have 9 targets; 8 of these, arranged in a circle, will be positioned 20 cm from its center, that is, the ninth target. The center of the target panel will be aligned with the shoulder acromion of the impaired upper limb. The distance between the participant and the center of the panel will be set according to each participant’s arm length measured with the fist closed. During the pointing task trials, the participants will be instructed to reach, at their self-selected speed, one of the 9 targets on the board.

All the participants enrolled in this study will perform assessment tasks in the hospitals’ premises.

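### The repeated ANOVA on which the trial is sized uses only complete T0-T1-T2 records; the mixed model already named should be made the primary FMA-UE analysis, in all randomised patients

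*Protocol article*

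**What the plan says.** All references are to the Protocol article.

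- **Primary outcome.** The Methods Overview states: "The primary outcome assessed at T2 will be assessed by the Fugl-Meyer Assessment-Upper Extremity (FMA-UE) scores". T1 is the mid-intervention visit, after the 7th session.
- **Test.** Under Analysis of the Effectiveness: "Treatment effects will be compared using a 2-way repeated ANOVA for clinical measurements, considering “time” (3 levels: T0, T1, and T2) as a within-subject factor", with the three arms as the between-subject factor.
- **Analysis set.** The primary outcome analysis "will be performed using the per-protocol principle".
- **Second method for the same period.** The same section adds: "Immediate training effects (data from T0-T2) and the durability of training effects (data from T2-T3) will be separately investigated using mixed effect models". It names no outcome for these models and does not rank them against the ANOVA.
- **Sample size.** The Sample Size section sizes the trial for a repeated ANOVA on the FMA-UE group by time interaction, with three groups, three measurements and 54 patients. Then, "when considering a dropout rate of 10%, we plan to recruit 20 participants for each group". It labels the three measurements T1, T2 and T3, whereas the analysis uses T0, T1 and T2. That mismatch needs reconciling but does not affect this point.
- **Place of assessment.** Under Assessment: Instrumental Setup: "All the participants enrolled in this study will perform assessment tasks in the hospitals’ premises".

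**The concern.** A classical repeated-measures ANOVA with a three-level time factor works on complete rows. A missing T1 or T2 removes the whole patient. This fits poorly with an endpoint placed at T2, because an absent mid-course score can take a patient out of the main comparison although the T2 score was obtained.

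Two things are at stake. One is precision: observed scores are thrown away in a trial of 60. The other is selection: if patients with little gain by T1 are the ones who fail to return, the remaining T2 mean is too favourable in that arm, and the comparison is distorted when arms differ in how many they lose. A difference is possible, since EG@Home patients are treated at home but assessed at the hospital. The article gives no evidence that it will occur.

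This is not the same as the per-protocol choice. An as-randomised set put through the same ANOVA would still lose the incomplete records.

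**Working it through.** **1. Reproduce the planned size.** Inputs from Sample Size: effect size 0.495, power 0.8, two-sided alpha 0.05, k = 3 groups, m = 3 measurements.

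Read 0.495 as Cohen f and test the interaction with df1 = (k-1)(m-1) = 4, df2 = (N-k)(m-1) and noncentrality N x f². The smallest N with power of at least 0.80 is 52, or 54 in equal groups. At N = 54: df2 = 51 x 2 = 102, noncentrality 54 x 0.495² = 13.23, power 0.825. Dropout: 54/0.9 = 60. Both stated figures reproduce.

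If 0.495 were a standardised mean difference (f = 0.495/2 = 0.2475), with noncentrality N x m x f²/(1-rho), the interaction would need 68 at rho = 0 and 48 at rho = 0.3. It would pass through 54 only at an intermediate correlation of about 0.21, and the article states no correlation. The reading that gives 54 without an added correlation is Cohen f, so 0.495 cannot be treated as an SD difference between arms.

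**2. Which records each method uses.**

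| Scores observed | Classical repeated ANOVA | Likelihood-based mixed model |
|---|---|---|
| T0, T1, T2 | used | used |
| T0, T2 (T1 missed) | patient dropped | T0 and T2 used |
| T0, T1 (T2 missed) | patient dropped | T0 and T1 used |

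**3. Precision, with the formula that reproduces 54.**

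- All 60 contribute: noncentrality 60 x 0.495² = 14.70, power 0.869. This is a ceiling for a mixed model, since a partial record carries less than a full one.
- 10% miss at least one visit: 60 x 0.9 = 54 complete records, power 0.825.
- T1 and T2 each missing independently in 10% (assumption): 60 x 0.9 x 0.9 = 48.6, about 49, power about 0.78.

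**4. Selection bias. All inputs here are assumptions.** Let X be the standardised T1 change, and let T2 be missed with probability expit(a - sX), where a is set to give the chosen dropout rate and s is the slope per SD. With correlation rho between T1 and T2 changes, the completer mean at T2 is too high by rho x E[X | retained]. By simulation at rho = 0.7, in SD of the T2 change:

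| Dropout in the arm | s = 0.5 | s = 1.0 | s = 1.5 |
|---|---|---|---|
| 5% | 0.018 | 0.033 | 0.045 |
| 10% | 0.035 | 0.063 | 0.085 |
| 20% | 0.068 | 0.121 | 0.159 |
| 20% minus 5% | 0.050 | 0.088 | 0.114 |

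The 20%/5%/5% split keeps the planned overall rate: 4 + 1 + 1 = 6 of 60 = 10%. The bias is proportional to rho. The low end is 0.050 x 0.5/0.7 = 0.036 (rho 0.5, s 0.5), and the high end is 0.114 x 0.8/0.7 = 0.130 (rho 0.8, s 1.5). The range is about 0.04 to 0.13 SD. With equal rates and the same mechanism in both arms, the two terms subtract to about zero.

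For scale, with 16 and 19 patients left, the standard error of an arm difference is sqrt(1/16 + 1/19) = 0.34 SD, so the central value of 0.088 SD is about a quarter of one standard error (0.088/0.34 = 0.26).

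This calculation covers loss of T2. A missed T1 alone is not simulated. If such misses are unrelated to outcome, they cost precision only.

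**The case against.** **The deletion is not written down.** The article names the test and is silent on missing visits, and an analysis plan that is not shown could add imputation. This stands as a limit: a reader might infer that the article states these patients will be dropped, and it does not. The point rests on the published choice of method, which needs complete rows unless something is added to it.

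**A mixed model is already planned.** A reader might take the word separately to mean that the mixed models stand apart from the primary test. The more natural reading is that it divides the T0-T2 question from the T2-T3 question. The models are therefore unranked, not clearly secondary. What remains is that two methods cover the same T0-T2 data, the trial is sized on the one that discards partial records, and nothing says which decides.

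**Most of the simulated bias belongs to the per-protocol set.** Patients who stop early would ordinarily be outside that set whatever the model. This is correct, and it means that replacing the model alone would not remove the bias. The loss specific to the ANOVA is then confined to adherent patients with a missed assessment.

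**Unequal dropout is speculation.** The split is 4, 1 and 1 patients, and no section supports it. Outpatients are eligible, so some patients in the hospital arms must travel for treatment as well as for assessment, and the imbalance could run the other way. This stands. The figures illustrate a mechanism and do not forecast it.

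**Conclusion.** The point holds as a choice of method that is worth changing. The repeated ANOVA on which the trial is sized uses only three-visit records, so it can discard a patient whose T2 primary endpoint was measured. The article names a method that avoids this and leaves its rank open.

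The size is modest. Against a ceiling of 0.869, power at the planned 54 complete records is 0.825, about 4 points lower, and the sample size already allows for that loss. The bias of 0.04 to 0.13 SD depends on an assumed 20% against 5% loss, dropout driven by the T1 change, correlation 0.5 to 0.8 and slope 0.5 to 1.5; it largely cancels under equal loss with the same mechanism.

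Two stronger conclusions might be inferred and are not supported. The bias should not be expressed as a share of 0.495, because the article does not state the metric and its 54 follows directly when 0.495 is Cohen f. Nor do the documents show that the home arm will lose more patients.

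**What to change.** Under Analysis of the Effectiveness:

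1. Make the mixed model for T0-T2 the primary FMA-UE analysis. Use all observed T0, T1 and T2 values; group, visit and group by visit; unstructured within-patient covariance; and REML with Kenward-Roger degrees of freedom.
2. Name the between-group contrast at T2 as primary, in line with the stated endpoint.
3. Apply it to all randomised patients and state that none is removed for a missed visit. Without this step, early dropouts stay excluded whatever the model.
4. Keep the complete-record or per-protocol repeated ANOVA as a sensitivity analysis.

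**Cost.** Wording only: no new visits, patients or measurements. The article reports recruitment closed in December 2022, so the change should be fixed and dated before group results are examined. The model relies on missing at random, and its degrees of freedom are approximate in a sample this small.

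### The primary outcome is FMA-UE at T2, but the planned test is a 4-df group-by-time interaction over T0–T2 with no T2 contrast fixed, and durability is modelled on T2–T3 without baseline

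*Protocol article*

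**What the plan says.** The Methods overview fixes outcome and visit: "The primary outcome assessed at T2 will be assessed by the Fugl-Meyer Assessment-Upper Extremity (FMA-UE) scores". T2 follows the 15th session, T1 follows the 7th, and T3 is a follow-up two months after the intervention, meant to assess maintenance and long-term effects.

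Under Analysis of the Effectiveness, "Treatment effects will be compared using a 2-way repeated ANOVA for clinical measurements". Time enters with "3 levels: T0, T1, and T2) as a within-subject factor" and group with "3 levels: EG@Hosp, EG@Home, and CG) as a between-subject factor". Post hoc comparisons use .05/3 = .017 and are described as comparing interaction effects, with no visit named.

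The same section then says that immediate effects (T0–T2) and "the durability of training effects (data from T2-T3) will be separately investigated using mixed effect models".

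The Sample Size section confirms that the target is the group-by-time interaction on FMA-UE, but lists a different set of visits: "number of measurements=3 [ie, T1, T2, and T3". It states that "an effect size of 0.495 [60,61] is expected based on previous studies" and that "a total sample size of 54 will be required for repeated ANOVA with a power of 0.8 and a 2-sided type-I error of 0.05".

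**The concern.** A trial whose primary outcome is a score at one visit needs a primary test of the group difference at that visit. The planned test asks something else: whether the three arms have the same shape over T0, T1 and T2. It can reject because of the mid-treatment visit alone, and the post hoc step does not bring the conclusion back to T2, because no visit is specified.

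Two further points leave the conclusion open. The T0–T2 data are analysed both by ANOVA and by mixed models, with no rule for which one decides if they disagree. And the durability analysis uses T2 and T3 only. If the gain is fully kept, the change from T2 to T3 does not differ between arms, so the hoped-for result is a null result. A null result also arises when there was no gain to lose, or when the test is too weak to see a loss.

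**Working it through.** **1. The plan's own figure.** For the interaction, df1 = (3−1)(3−1) = 4 and df2 = (54−3)(3−1) = 102. The stated total of 54 cannot be reproduced from the stated inputs alone, because neither the effect-size metric nor the between-visit correlation is given. Read as Cohen's f = 0.495 with correlation 0.5, 12 patients would be enough. Read as d = 0.495 with evenly spaced arms, f = 0.495/√6 = 0.202. With correlation 0.5, λ = 0.202² × 54 × 3/0.5 ≈ 13.2, and power is 0.825 at 54 and 0.798 at 51, so 54 is the smallest balanced total under that reading. The dropout step is right: 54/0.9 = 60.

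**2. Assumptions for the checks (not in the documents).** 18 completers per arm; 0.495 read as a standardised mean difference d; the same benefit in both AOT arms and none in control; normal data; compound symmetry with correlation ρ of 0.6, 0.7 or 0.8.

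The arm profile (1, 1, 0) has centred sum of squares 2/3, and 18 × 2/3 = 12. Also d² = 0.245.

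- 4-df interaction: λ = 12 × SS/(1−ρ), where SS is the centred sum of squares of the effect over T0, T1, T2.
- Baseline-adjusted T2 test (2 and 50 df): λ = 12 × d²/(1−ρ²). This ignores chance baseline imbalance, so it is very slightly optimistic. With complete data it stands in for the T2 comparison from a mixed model.

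**3. Effect at T1 only, none at T2.** Profile (0, d, 0), SS = (2/3)d² = 0.163.

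| ρ | 0.6 | 0.7 | 0.8 |
|---|---|---|---|
| λ, 4-df test | 4.90 | 6.53 | 9.80 |
| 4-df test rejects | 37% | 49% | 68% |
| T2 test rejects | 5% | 5% | 5% |

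Simulation gives 36–70% over the same range. With larger effects relative to the correlation (0.75 SD at ρ = 0.7, or 0.43 SD at ρ = 0.9) the 4-df test rejects in about 87% of trials.

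**4. Power when there is an effect at T2.**

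| ρ | 0.6 | 0.7 | 0.8 |
|---|---|---|---|
| Half the effect at T1: SS = d²/2, λ | 3.68 | 4.90 | 7.35 |
| 4-df test | 28% | 37% | 54% |
| All or none at T1: SS = (2/3)d², 4-df test | 37% | 49% | 68% |
| T2 test: λ | 4.59 | 5.77 | 8.17 |
| T2 test, 2 df at .05 | 44% | 54% | 70% |
| One AOT–control contrast at .05/3 | 28% | 35% | 50% |

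The last row uses noncentrality d/√((2/18)(1−ρ²)) = 1.86, 2.08, 2.48. In simulation the even build-up gives 28/39/55% against 43/55/69%, a gain of 14–16 points. With all or none of the effect at T1, the gain is 1–7 points.

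Under serial correlation (AR 0.85 with 0.75 SD; AR 0.95 with 0.43 SD), the Greenhouse–Geisser-corrected 4-df test against the T2 test gives 0.86 vs 0.91 and 0.84 vs 0.86 with half the effect at T1. With all or none at T1 it gives 0.96 vs 0.91 and 0.95 vs 0.85–0.86, so the order reverses.

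**5. Durability.** For the T2–T3 group-by-time test (2 and 51 df), λ = 12 × (loss)²/(2(1−ρ)).

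| ρ | 0.6 | 0.7 | 0.8 |
|---|---|---|---|
| Gain fully kept | 5% | 5% | 5% |
| Half lost (0.2475 SD): λ | 0.92 | 1.23 | 1.84 |
| Half lost: detected | 12% | 15% | 20% |
| All lost (0.495 SD): λ | 3.68 | 4.90 | 7.35 |
| All lost: detected | 37% | 47% | 65% |

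A T3 group comparison without T0 has λ = 12 × 0.245 = 2.94 and 30% power for a fully kept gain. Adjusted for T0, λ and power are those of the T2 test in step 4: 44%, 54% and 70%.

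**The case against.** The repeated ANOVA is a valid test, and the trial was sized on it. Because T0 is a level of time, the interaction already compares change from baseline between arms, and the T0-to-T2 change is one of its components. A reader might infer that the analysis ignores baseline or averages T1 into T2. It does neither; what it lacks is a baseline covariate, and in a randomised trial that costs precision without causing bias. This part of the objection stands.

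A reader might also infer that the planned test loses power in general. It does not. The clear advantage of the T2 test appears when the effect builds evenly under compound symmetry. It shrinks or reverses in the other settings of steps 4, and a single AOT–control contrast at .017 has no more power than the 4-df test.

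On durability, the article does not list the terms of the T2–T3 model and nowhere says that a null change will be read as maintenance. A T3 group contrast could be taken from that model, so the claim that it cannot show durability would go too far. Such a contrast would lack T0 and be inefficient.

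Handling of patients with a missed visit is commonly left to the analysis plan, and the T0–T2 mixed models can use incomplete records, so it is no part of this point.

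None of this meets the central point. The Methods overview names T2, and nothing in the analysis section ties a between-group test to it.

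**Conclusion.** The point holds as a mismatch between endpoint and test. The 4-df interaction can be significant with no group difference at T2, in about 36–70% of trials under the assumptions in step 2, against about 5% for a T2 test. The article also leaves open which T0–T2 analysis decides, and its T2–T3 analysis omits baseline, so a non-significant change is not evidence that an advantage over control persists.

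The sizes rest on a metric for 0.495 and on correlations that the documents do not give. The mismatch itself does not depend on them. The argument for change is the match to the endpoint, with power secondary and conditional. This should be fixed, but it does not make the planned analysis invalid.

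**What to change.** Name one primary analysis: a mixed model with FMA-UE at T1, T2 and T3 as outcomes, T0 FMA-UE as covariate, and group, visit and group-by-visit terms.

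- **Primary result:** the between-group comparison at T2, as a 2-df group test at .05, followed by the three pairwise contrasts at the .017 already stated.
- **Durability:** the T3 contrast of each AOT arm against control, from the same model.
- **Supportive only:** the repeated ANOVA and the separate T2–T3 model. State that the new model replaces the separate T0–T2 mixed model.

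No new visits or measurements are needed. The cost is that the analysis departs from the interaction on which the trial was sized. The Sample Size section must therefore be aligned, including its visit set (T1, T2, T3 there; T0, T1, T2 in the analysis), the effect-size metric and the assumed correlation. Power for the T2 comparison should be reported honestly for the patients available. Under the Ethics Approval section, deviations need notification and approval before they are applied, so this has to be settled before outcome data are analysed. The article reports recruitment closed in December 2022 and results expected in spring 2023. It does not say that all outcome data are in, so a reader should not assume either that the change is mere rewording or that it is too late.
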